### Safety monitoring and adverse event reporting

2.9

#### Observation periods

2.9.1

Three-tiered safety observation windows:

Single-session phase: From intervention initiation to 24 h post-procedure.

Full intervention phase: From first treatment to T1 follow-up.

Extended follow-up phase: T1 to T2 follow-up.

#### AE classification and reporting

2.9.2

AE documentation: All adverse events graded (Grade 1–5) per CTCAE v5.0 criteria.

SAE reporting: Defined as events causing death, life-threatening conditions, hospitalization, or permanent disability, requiring immediate (<24 h) reporting to Ethics Committee of Sichuan integrative medicine hospital.

Causality assessment: WHO-UMC causality categories applied (certain/probable/possible/unrelated).

#### Statistical analysis

2.9.3

Incidence rate: AE incidence = (Number of AE episodes / Total treatment sessions) × 100%.

Severity stratification:

Grade 1–2: Mild, requiring no intervention.Grade ≥ 3: Mandating medical intervention or protocol modification.

Temporal analysis: Time-to-event analysis using Cox proportional hazards model.

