**Methods/design:**

This double-blind randomized controlled trial will enroll 60 elderly patients (60–85 years) meeting ICSD-3 criteria for CI and Rome IV criteria for FD. Using block randomization with computer-generated sequences, eligible participants will be allocated 1:1 to either active taVNS group (*n* = 30) or sham control group (*n* = 30). The CFDA-certified transcutaneous vagus nerve stimulator (Model tVNS501, Reach Medical, China; Registration No. SuXieZhun20212090050) will be positioned at standardized anatomical sites: the concha cymba (the inferior margin of the intersection between the superior and inferior crura of the antihelix within the cymba conchae), electrical stimulation will deliver with fixed parameters (frequency: 80 Hz, pulse width: 100 μs, pulse 40–60s). The active group will receive validated taVNS parameters, while the sham group will undergo identical procedures without electrical output. Interventions will be administered 30 min per session, 5 sessions weekly for 3 consecutive weeks. Primary endpoints include changes in Pittsburgh Sleep Quality Index (PSQI) and Nepean Dyspepsia Symptom Index (NDSI) at week 3. Secondary outcomes encompass Insomnia Severity Index (ISI), 36-Item Short Form Survey (SF-36), and serum biomarkers (pro-inflammatory cytokines IL-1*β*, IL-4, IL-6, TNF-*α*, hs-CRP, TGF-β; neurotransmitters Dopamine (DA), serotonin (5-hydroxytryptamine, 5-HT), norepinephrine (NE), Glutamate (Glu), *γ*-aminobutyric acid (GABA)). Safety profiles will be systematically evaluated using CTCAE v5.0 criteria, with all adverse events documented throughout the study.

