### Randomization and blinding

2.6

The randomized controlled trial (RCT) utilized a simple randomization method implemented via the PROC PLAN procedure in SAS 9.4 software, which was designed by an independent statistician. A fixed seed number of 60 was preset to ensure reproducibility, and participants were allocated to the two groups (30 each) at a 1:1 ratio, with random numbering from 01 to 60, generating 60 unique sequences to ensure unbiased group allocation. The group allocation information was sealed in tamper-evident opaque envelopes and managed by a blinded study coordinator who was not involved in participant recruitment or outcome assessment, ensuring strict allocation concealment.

During trial execution, consecutively enrolled participants meeting inclusion criteria were sequentially assigned unique identification numbers. The blinded trial coordinator strictly adhered to the enrollment chronology when unsealing pre-sequenced, tamper-evident sealed envelopes. The revealed allocation information was subsequently transferred to an independent investigator uninvolved in recruitment or intervention delivery, who executed group assignments per the predefined randomization matrix. The study protocol explicitly prohibited any deviation from allocation sequences or non-programmatic modifications.

The independent researcher, based on randomized allocation, preset the transcutaneous auricular vagus nerve stimulator (tVNS501) with fixed parameters (intensity: 20–40 mA, frequency: 80 Hz, pulse width: 100 μs, pulse 40–60s) and blinded the display screen using opaque tape before handing it to a clinical operator. In the active stimulation group, the device was powered to deliver real stimulation, while in the sham stimulation group, the device remained inactive (no current output) but maintained physical contact. A triple-blind design (participant-operator-outcome assessor) was implemented throughout the study to maintain blinding of group assignment (taVNS or sham taVNS). Unblinding was performed post-database lock by an independent statistician using SAS 9.4 (SAS Institute Inc., Cary, NC), strictly adhering to the predefined protocol. This study strictly adhered to the principle of observer independence in clinical research (Figure 1).

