### Intervention

2.7

Following standardized screening, all participating clinicians underwent unified training in both taVNS and sham taVNS protocols. The informed consent form explicitly stated that the study involved two distinct neuromodulation interventions (which may differ in electrical sensation and therapeutic responses). Training modules included: (1) Device operation: standardized procedures for power cycling and locked parameter interfaces; (2) Anatomical localization: precise electrode placement at the tragus: the inferior margin of the intersection between the superior and inferior crura of the antihelix within the cymba conchae and the junction of the inferior crus of the antihelix and the auricle within the cymba conchae using auricular anatomical charts; (3) Blinding maintenance: standardized communication protocols to prevent unintentional disclosure of group allocation. All interventions were conducted in standardized treatment rooms within the hospital inpatient department.

All clinicians participating in this study were required to have at least 2 years of standardized acupuncture practice. Participants were placed in a supine position, and the auricular stimulation areas were cleaned with 75% ethanol solution followed by placement of ear clips. The clinically trained operator, blinded to group assignment, using transcutaneous auricular vagus nerve stimulators (tVNS501), precisely placed bipolar electrodes at standardized anatomical sites: the concha cymba (the inferior margin of the intersection between the superior and inferior crura of the antihelix within the cymba conchae). The intervention protocol consisted of 30-min sessions, administered weekdays from 9:00 to 11:00 AM for three consecutive weeks (15 sessions total).

Participants shall be withdrawn from the trial and provided with appropriate medical interventions under any of the following circumstances: (1) occurrence of serious adverse events; (2) voluntary withdrawal request from the participant; (3) clinical deterioration of the underlying condition; (4) requirement for prioritized treatment of other medical disorders; or (5) development of localized irritation or allergic reactions.

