#### Statistical analysis

2.8.5

Primary analyses were conducted using the intention-to-treat (ITT) dataset, defined as the subset of participants who completed ≥1 intervention session, baseline assessment, and ≥ 1 post-baseline evaluation. In accordance with CONSORT guidelines, missing data were handled via multiple imputation (R package ‘mice’ v3.14.0). Sensitivity analyses were performed using the per-protocol set (PPS) to validate robustness.

The per-protocol set (PPS) followed ICH E9 guidelines with three integrated criteria: protocol compliance requiring 80–120% intervention dose completion, avoidance of prohibited medications, and key visit time deviations ≤3 days; data integrity enforcing <5% missingness in CDISC ODM v2.1-compliant CRF fields and laboratory CV% <15; and analytical scope restrictions that included cases with complete demographic/clinical data for baseline analysis, excluded efficacy cases with blinded-independent-adjudication-confirmed major protocol deviations (MPDs), while employing a modified PPS (mPPS) for safety analysis to retain participants discontinuing due to adverse events (AEs).

Post-trial, an independent third-party observer (uninvolved in study design or intervention delivery) performed the following: (1) Baseline data collection: Including gender, age, disease duration (months), BMI, education level, occupation category, marital status, and dietary patterns; (2) Outcome measures collection: Primary outcomes: Pittsburgh Sleep Quality Index (PSQI) and Nepean Dyspepsia Symptom Index (NDSI);Secondary outcomes: Insomnia Severity Index (ISI), 36-Item Short Form Health Survey (SF-36), inflammatory biomarkers (e.g., IL-6, CRP), and neurotransmitter levels (e.g., 5-HT, GABA); (3) Data de-identification: Removal of all direct or indirect identifiers (e.g., name, ID number), with assignment of unique study IDs.

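### Adverse events are counted per treatment session, not per participant, and safety is analysed on a modified per-protocol set instead of all treated participants

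*Protocol article*

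**What the plan says.** **Measure.** Section 2.9.3 of the protocol article, under a label that calls it an incidence rate, gives "AE incidence = (Number of AE episodes / Total treatment sessions) × 100", expressed in percent. The same section plans severity strata and a Cox time-to-event analysis, but states neither the event nor the analysis set for the Cox model. The article defines no proportion of participants with at least one AE.

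**Exposure.** Section 2.7 has sessions "administered weekdays from 9:00 to 11:00 AM for three consecutive weeks (15 sessions total". The abstract agrees: "Interventions will be administered 30 min per session, 5 sessions weekly for 3 consecutive weeks". Section 2.6 states that "participants were allocated to the two groups (30 each) at a 1:1 ratio".

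**Windows.** Section 2.9.1 sets three safety windows: the 24 hours after a session, the treatment course to T1, and "Extended follow-up phase: T1 to T2 follow-up". Section 2.9.3 does not say which of these the formula covers.

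**Analysis set.** Section 2.8.5 describes "employing a modified PPS (mPPS) for safety analysis to retain participants discontinuing due to adverse events (AEs". The per-protocol set that this modifies requires "protocol compliance requiring 80–120% intervention dose completion, avoidance of prohibited medications, and key visit time deviations ≤3 days" and "data integrity enforcing <5% missingness in CDISC ODM v2.1-compliant CRF fields", among other criteria. The article nowhere defines a safety set of all treated participants.

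**Monitoring.** Section 2.10 lists an SAE incidence above 10% as an example of a trigger for an emergency safety board meeting. It does not say how that incidence is counted.

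**The concern.** Most readers take an AE incidence in percent as the share of participants who had an event. A count of episodes over sessions answers a different question, and in a 15-session course it is usually a much smaller number. The abstract's objective presents the treatment as safe and well tolerated in patients aged 60 to 85, so the headline safety figure will carry weight.

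The analysis set adds a second problem. A per-protocol set selects on what happens after randomisation: sessions completed, drugs taken, visits kept, data returned. Those can all be related to tolerability. Keeping participants who stop because of AEs removes the most obvious part of that selection, but the text does not lift the remaining criteria for safety.

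**Working it through.** **Inputs**
- Sessions per participant: 15 (section 2.7). Check against the abstract: 5 per week × 3 weeks = 15, so the plan's figure is reproduced.
- Participants per arm: 30 (section 2.6).
- Planned sessions: 30 × 15 = 450 per arm; 60 × 15 = 900 in total.
- Per-protocol dose floor: 80% of 15 = 12 sessions (section 2.8.5).
- Expected dropout: 5–10% (section 2.5), that is 3 to 6 of 60.

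**Gap between the two measures.** Let K of N participants have at least one AE, with E episodes in all over S sessions. Then

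participant share ÷ session figure = (K/N) ÷ (E/S) = (S/N) ÷ (E/K),

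which is mean sessions per participant divided by mean episodes per affected participant. The numbers of affected participants below are illustrations; the article gives no expected AE rate.

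| Scenario, one arm of 30 | Participant share | Section 2.9.3 figure | Factor |
|---|---|---|---|
| 9 affected, 1 episode each | 9/30 = 30% | 9/450 = 2.0% | 15 |
| 30 affected, 1 episode each | 30/30 = 100% | 30/450 = 6.7% | 15 |
| 6 affected, 1 episode each | 6/30 = 20% | 6/450 = 1.3% | 15 |
| 6 affected, 1 each, all stopping after session 3 | 20% | 6/(24 × 15 + 6 × 3) = 6/378 = 1.6% | 12.6 |
| 6 affected, 2 episodes each | 20% | 12/450 = 2.7% | 7.5 |
| 6 affected, 5 episodes each | 20% | 30/450 = 6.7% | 3 |
| 6 affected, 15 episodes each | 20% | 90/450 = 20% | 1 |

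The factor depends on repeat episodes and completion, so a reader cannot recover the participant share from the reported figure.

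**Window.** No sessions are given between T1 and T2. An event in that period is either divided by sessions from an earlier period or has no denominator. The text does not say which, or whether such events are counted in the formula at all.

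**Analysis set.** Section 2.7 foresees withdrawal at the participant's request. Someone who does this after, say, 8 sessions has been exposed, falls short of 12 sessions, and has not stopped because of an AE. The single stated exception does not reach that person. The same reasoning applies to a treated participant who takes a prohibited drug. The number affected cannot be derived. The 3 to 6 expected dropouts give only an order of magnitude, because some may stop because of AEs and be kept, while prohibited medication does not require dropping out.

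**Monitoring trigger, if it used the section 2.9.3 formula.** Exceeding 10% would take more than 0.10 × 900 = 90 SAEs over the full trial. One SAE in every participant would give 60/900 = 6.7%. Counted by participants, 7/60 = 11.7% already exceeds it.

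**The case against.** The strongest defence of the formula is that it is openly a rate. Section 2.9.3 labels it so and shows both its parts, and episodes per session is a recognised exposure-based measure for a device used repeatedly. Both arms have the same planned number of sessions, so with similar completion the comparison of episode counts between arms is preserved. This stands as a defence of keeping the rate. It does not make the rate a substitute for the participant proportion, and the percent sign and the word incidence invite that reading.

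A reader might infer that harm will be understated 15-fold. The documents support only a ceiling of 15. Local irritation, which section 2.7 names as a withdrawal reason, could recur over sessions and would shrink the factor.

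A reader might also infer that events between T1 and T2 are in the numerator. Section 2.9.3 does not say so; the formula could be meant for the single-session window alone. What stands is the ambiguity.

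On the analysis set, section 2.8.5 does not state which other per-protocol criteria carry over to safety, and it ties the exclusion for major protocol deviations to efficacy. So a flat statement that everyone below 12 sessions for a non-AE reason is removed goes further than the text. Two possible examples are weak: clinical deterioration could itself be recorded as an AE, and the laboratory variation limit reads as an assay-precision criterion. Nor do the documents show that those left out would be the participants with the most harm.

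Finally, all AEs are documented, SAE reporting is not tied to the modified set, and a Cox model is planned. Documentation preserves the data but does not fix the summary. The Cox model has no stated event or set and does not replace a proportion. A separate analysis plan may fill in detail, but the formula and the choice of a per-protocol base are stated here.

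**Conclusion.** The concern holds. As written, the only defined AE frequency is a per-session percentage that can be up to 15 times below the share of participants affected, and the safety set is not all treated participants. The factor of 15 assumes full completion and one episode per affected participant. It is 12.6 in the early-stopping example, 7.5 with two episodes each and 3 with five.

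The possible exclusion of treated participants rests on the name of the set and its single stated exception, and its size is unknown. The point about the safety board trigger is conditional on its using the same formula: a reader might infer that the trigger could hardly ever be met, but section 2.10 does not say which definition applies. Efficacy analyses are not affected.

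**What to change.** Before unblinding:

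1. **Section 2.8.5:** replace the modified per-protocol set for safety with all participants who received at least one session, analysed by treatment received.
2. **Section 2.9.3:** make the main safety measure the number of participants with at least one AE divided by participants treated, per arm, with exact 95% confidence intervals and the arm difference.
3. **Section 2.9.3:** keep episodes per session only as a supplementary rate, labelled as such and limited to the single-session window.
4. **Section 2.10:** state which definition of incidence the SAE trigger uses.

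The cost is wording in three sections. No new data are needed, because all AEs are already to be recorded. The reported AE percentages will generally look larger than under the present formula.

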### Data safety monitoring protocol

2.10

An independent Data Safety Monitoring Board (DSMB) was established, comprising clinical specialists, biostatisticians, methodological experts, and ethicists (all members provided signed conflict-of-interest declarations). The DSMB conducts dynamic safety surveillance through scheduled 24-week meetings and emergency sessions triggered by predefined thresholds (e.g., >10% SAE incidence at any site or > 20% participant dropout rate).

Adverse events were classified into four tiers per CTCAE v5.0 criteria: Grade 1 (asymptomatic/mild symptoms requiring monitoring), Grade 2 (interruption of intervention ≤7 days with symptomatic treatment), Grade 3 (intervention termination and multidisciplinary consultation), and Grade 4 (immediate emergency care and permanent withdrawal).

All SAEs were reported within 12 h (life-threatening) to 24 h (non-critical). Full compliance with Council for International Organizations of Medical Sciences (CIOMS) VI standards for Suspected Unexpected Serious Adverse Reaction (SUSAR) reporting was maintained, with critical protocol amendments requiring ≥75% approval via anonymous voting.

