### Settings and subjects

2.1

This randomized controlled trial (RCT) was conducted at the Sichuan integrative medicine hospital (Chengdu, Sichuan, China). The study protocol (Version 2.0, dated March 14, 2024) strictly adhered to the ethical principles of the Declaration of Helsinki and was approved by the Clinical Research Ethics Committee of the Sichuan Provincial Hospital of Integrated Traditional Chinese and Western Medicine (Approval No.: KY-2024-001; Date: March 18, 2024).

In accordance with the International Standards for Clinical Trial Registration (ICTRP), the research team prospectively registered the trial at the Chinese Clinical Trial Registry on February 2, 2024 (Website: www.chictr.org.cn; Registration No.: ChiCTR2400080630).

In compliance with ethical requirements, researchers provided detailed explanations of the study objectives, procedures, and potential risks to all participants. Informed consent was obtained from each participant after ensuring their full understanding of the study, and participants retained the right to withdraw unconditionally at any time. The first participant was formally enrolled on July 26, 2024, marking the commencement of the study’s implementation phase.

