### Sample size estimation

2.5

Based on existing RCT literature, the efficacy rate of taVNS in treating elderly patients with CI ranges from 73.3 to 93.3% (21, 22), while its efficacy in FD reaches 92.3% (3). Building upon our preliminary exploratory clinical study involving 10 cases, we observed an 80.0% efficacy rate (*p* < 0.01) for taVNS in treating elderly patients with CI comorbid with FD, demonstrating significant clinical effectiveness.

This study employed a superiority trial design and utilized PASS 2021 software (NCSS LLC, Kaysville, USA) for prospective sample size estimation. Based on clinical data reported in reference (23), with anticipated efficacy rates of 20% in the sham stimulation group and 70% in the active stimulation group, we conducted a two-independent proportion *z*-test analysis with the following parameters: type I error probability *α* = 0.05, statistical power 1-*β* = 0.99, and 1:1 allocation ratio. Through Monte Carlo simulation validation, the minimum theoretical sample size was calculated as 28 participants per group.

In accordance with CONSORT Statement guidelines regarding dropout rates and considering our institutional clinical practice experience with anticipated 5–10% dropout rates, we ultimately determined to enroll 30 participants per group (total *N* = 60). This sample size enables detection of a Cohen’s *h* effect size of 0.99 (Power = 0.991, 95% CI 0.89–1.07), satisfying the statistical power requirements for superiority trials.

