##### Pittsburgh sleep quality index (PSQI)

2.8.2.1

Assessment timepoints: Baseline (T0), post-intervention (T1, week 3), and follow-up (T2, week 4 post-treatment).

Evaluation domains: Seven components including subjective sleep quality, sleep latency, and sleep duration.

Scoring system: Total scores range from 0 to 21, with ≥8 indicating sleep disturbance. A change ≥3 points was considered clinically significant.

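### The two DSMB emergency triggers named in section 2.10 ignore arm in a one-hospital trial, so up to 20% SAEs or 40% dropout confined to active stimulation crosses neither

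*Protocol article*

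**What the plan says.** - **Section 2.10 (Data safety monitoring protocol)** sets calendar meetings and gives two emergency triggers as examples: "scheduled 24-week meetings and emergency sessions triggered by predefined thresholds (e.g., >10% SAE incidence at any site or > 20% participant dropout rate". Arm is not mentioned in either.
- **Section 2.1 (Settings and subjects)** names a single centre; the trial "was conducted at the Sichuan integrative medicine hospital".
- **Section 2.6 (Randomization and blinding)** allocates 30 participants to each arm, describes a sham device that delivers no current, and states one time for opening the codes: "Unblinding was performed post-database lock by an independent statistician using SAS 9.4". It mentions no earlier release to the DSMB.
- **Section 2.5 (Sample size estimation)** plans for "anticipated 5–10% dropout rates, we ultimately determined to enroll 30 participants per group".
- **Sections 2.7 and 2.8.2.1** give 15 sessions over three weeks, with assessments at "post-intervention (T1, week 3), and follow-up (T2, week 4 post-treatment". Each participant is therefore followed for about seven weeks.
- **Section 2.9.3** defines AE incidence as episodes over total treatment sessions, not as participants affected.
- **Sections 2.9.2 and 2.10** require each SAE to be reported individually, within 12 to 24 hours according to 2.10. Section 2.9.2 names the ethics committee as recipient.

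**The concern.** In a sham-controlled device trial, the DSMB's particular task is to notice harm that is more frequent under stimulation than under sham. A per-site trigger cannot separate anything when there is one site. As written it is a rate over all participants, and an excess confined to the active arm is halved before it meets the threshold. The dropout trigger, "> 20% participant dropout rate", is also written over participants without reference to arm, although early withdrawal can itself be a sign of poor tolerability.

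The scheduled meetings may not make up for this, because they are far apart relative to a three-week treatment. At stake is how early the DSMB would be convened to look at an imbalance between arms.

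**Working it through.** **Inputs.** 30 per arm and 60 in total (2.5, 2.6); triggers above 10% and above 20% (2.10); one site (2.1); 3-week treatment with 15 sessions (2.7); planned dropout 5–10% (2.5). The trigger percentages are set values with no derivation to reproduce. The denominator of 30 rests on the stated minimum of 28 per group, which does reproduce: (1.960 + 2.326)² × (0.20×0.80 + 0.70×0.30) / 0.50² = 27.19, rounded up to 28.

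**1. Ceilings with no sham events.**
- SAE: 6/60 = 10.0%, which does not exceed 10%. If all six are active, 6/30 = 20.0% vs 0/30 (Fisher exact, two-sided, p = 0.024). The seventh participant crosses the threshold.
- Dropout: 12/60 = 20.0%, which does not exceed 20%. If all twelve are active, 12/30 = 40.0% vs 0/30 (p = 0.0001). The thirteenth crosses.
- The same ceilings hold earlier at balanced counts; for example 3/30 overall = 3/15 active = 20%.

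**2. Ceilings with sham events.**
- SAE: with 1, 2 or 3 sham participants affected, the active ceiling is 5/30 = 16.7%, 4/30 = 13.3% or 3/30 = 10.0%.
- Dropout: 5–10% of 30 is 1.5 to 3, so 2 or 3 sham dropouts. The active ceiling is then (12 − 2)/30 = 33.3% or (12 − 3)/30 = 30.0%.

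**3. Chance that the SAE trigger is crossed.** The risks are assumptions; the documents give none. The single look sums Bin(30, active risk) and Bin(30, sham risk) at full enrolment: at least 7 of 60 for the whole-trial rule, at least 4 of 30 for the active arm. The running check is simulated (100,000 trials, random order, 30 per arm), with the rate examined after each participant from the 10th or the 30th enrolled; the by-arm rule counts a crossing in either arm.

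| Assumed SAE risk, active / sham | Check | Whole-trial rule | By-arm rule |
|---|---|---|---|
| 15% / 1% | single look at 60 | 0.20 | 0.68 (active arm) |
| 15% / 1% | running, from 30th | 0.47 | 0.88 |
| 15% / 1% | running, from 10th | 0.62 | 0.93 |
| 3% / 3% | running, from 30th | 0.03 | 0.23 |
| 3% / 3% | running, from 10th | 0.13 | 0.47 |

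The last two rows show the price: where the arms do not differ, the by-arm rule alerts more often.

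**4. Unit of the SAE rate.** If the per-session denominator of 2.9.3 applied, there would be 60 × 15 = 900 sessions and more than 90 SAE episodes would be needed. Steps 1 to 3 use participants, the reading more favourable to the plan.

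**5. Meeting interval.** Accrual is not stated. Assume a first meeting 24 weeks after the first enrolment and constant accrual of r per week. About r × (24 − 3) participants have then finished treatment: 10.5 at 0.5 per week, 31.5 at 1.5 per week, 52.5 at 2.5 per week. At the last rate all 60 (2.5 × 24) are already enrolled.

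**The case against.** Several points on the other side stand.

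- **The article is condensed.** The thresholds are introduced as examples, so others may exist, and data access or denominators may sit in a DSMB charter or the full protocol. A reader might infer from 2.6 that the DSMB has no route to data by arm. The document does not say that: the sentence concerns unblinding of the trial and leaves DSMB access undescribed. Section 2.8.4 also shows that A/B labels exist on the blood tubes during the trial.
- **SAEs are reported one by one.** A reader might infer that a 20% SAE rate could build up with no review at all. That is not supported: each event is reported within 12–24 hours, assessed for causality (2.9.2) and followed by withdrawal (2.7). What may fail to happen is an emergency DSMB session under these two thresholds. Case reports do not compare arms, however, and do not cover dropout.
- **The ceilings are extremes.** They need zero sham events, and a running rate is crossed more often than a single look at 60 suggests. Both are allowed for above.
- **Dropout against sample size.** A reader might infer that the 20% trigger must match the allowance from 30 down to 28 per arm. It need not, since the two serve different purposes. The power cost is also small: with 18 active and 30 sham, 0.50 / √(0.21/18 + 0.16/30) − 1.96 = 1.87, a power of about 0.97.

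None of this gives the per-site wording a function in a one-hospital trial or brings arm into either named trigger. Even a DSMB that sees arm data would be called early, under these two triggers, only by rates that ignore arm.

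**Conclusion.** The point holds in limited form. Both named emergency triggers are silent on arm, and the SAE trigger is in effect a whole-trial rate in which half the participants receive no current. The largest active-arm rates that cross neither are 20% for SAEs and 40% for dropout with no sham events, and 30–33% for dropout when sham loses the planned 5–10%. Under assumed SAE risks of 15% and 1%, a running whole-trial check is crossed with probability about 0.47–0.62, against about 0.88–0.93 by arm: detection is weakened, not absent.

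These figures assume a per-participant rate and no triggers beyond the two named. The effect of the 24-week interval depends on accrual and cannot be fixed from the document. This should be corrected as a specific gain in safety monitoring at small cost; it does not show that the trial lacks safety oversight.

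**What to change.** 1. **Section 2.10:** replace the per-site wording with the rate within each randomised arm, for SAEs and for dropout, counted as participants with at least one event over participants treated in that arm. Reconcile this with the per-session denominator in 2.9.3. Keep the stated percentages, as prompts for DSMB review only.
2. **Section 2.6:** state that before database lock the independent statistician gives arm-coded safety tables to the DSMB alone, and that everyone else stays blinded until lock.
3. **Section 2.10:** tie at least one DSMB review to enrolment, in addition to the calendar meetings.

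The cost is protocol and charter wording plus short safety tables from a statistician already in place. By-arm triggers fire more often by chance: at an equal 3% SAE risk, about 0.47 against 0.13 when checked from the 10th participant, or 0.23 against 0.03 from the 30th. A fired trigger leads only to a review.

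### Sections 2.9.2, 2.9.3 and 2.10 define adverse-event grade in incompatible ways under one CTCAE v5.0 label, so the Grade ≥3 stratum may partly reflect management decisions instead of severity.

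*Protocol article*

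**What the plan says.** Three sections of the protocol article describe adverse-event grade.

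- Section 2.9.2 (AE classification and reporting): "AE documentation: All adverse events graded (Grade 1–5) per CTCAE v5.0 criteria". The same section counts death among serious adverse events.
- Section 2.9.3 (safety statistics) forms two severity strata. Grades 1–2 are called mild and in no need of intervention. The upper stratum reads "Grade ≥ 3: Mandating medical intervention or protocol modification".
- Section 2.10 (Data safety monitoring protocol): "Adverse events were classified into four tiers per CTCAE v5.0 criteria: Grade 1 (asymptomatic/mild symptoms requiring monitoring), Grade 2 (interruption of intervention ≤7 days". The sentence goes on to attach treatment of symptoms to Grade 2, stopping of the stimulation plus a consultation across disciplines to Grade 3, and emergency care plus permanent withdrawal to Grade 4. The list ends there.

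Section 2.7 (Intervention) also matters. It requires withdrawal from the trial, with appropriate medical care, in five circumstances. The last is "5) development of localized irritation or allergic reactions", with no severity threshold.

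**The concern.** A severity grade should describe the event. What was then done about it is a separate fact, and it depends on the protocol's rules and the clinician's judgement. Section 2.10 gives a CTCAE grade number to a set of actions, and 2.9.3 defines its upper stratum by whether action was required. Two people coding the same event from different sections could reach different grades, and both could cite the article.

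The Grade ≥3 split is the only severity stratification that the article specifies, and safety is one of its main claims for the device. If grade carries the management decision, a table of Grade ≥3 events by arm cannot be read as a table of severe events.

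**Working it through.** The article gives no event counts, so no published figure can be reproduced. The check sets the definitions side by side and runs two cases through them.

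| Level | 2.9.2 | 2.9.3 | 2.10 |
|---|---|---|---|
| 1 | CTCAE v5.0 grade | lower stratum: mild, no intervention needed | symptoms: none or mild, monitored |
| 2 | CTCAE v5.0 grade | lower stratum, same description | action: pause of up to 7 days, symptoms treated |
| 3 | CTCAE v5.0 grade | upper stratum: action required | action: stimulation stopped, consultation held |
| 4 | CTCAE v5.0 grade | upper stratum, same description | action: emergency care, permanent withdrawal |
| 5 | CTCAE v5.0 grade | upper stratum, same description | no tier |

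**Counts.** There are five levels in 2.9.2 and four in 2.10, both attributed to CTCAE v5.0. Three of the four tiers in 2.10 (Grades 2, 3 and 4) are described by actions.

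**Case A: an event handled by a short pause and treatment of symptoms.** By its number in 2.10 it is Grade 2 and goes to the lower stratum of 2.9.3. By the description in 2.9.3 it cannot go there, because that stratum is for events needing no intervention. The same description arguably puts it in the upper stratum. The number and the description point to different strata.

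**Case B: mild irritation at the ear clip.** Section 2.7 requires withdrawal, whatever the severity.

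- Graded by severity under 2.9.2, the event could be Grade 1 or 2.
- Under 2.10, stopping the stimulation meets one of the two elements of Grade 3. The other, the consultation, is not required by 2.7, so the event does not fully qualify on the text.
- Under the wording of 2.9.3, withdrawal with medical care arguably meets the description of the upper stratum, with no consultation needed.

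**Scale.** Planned enrolment is 30 per arm. If the stratum is reported per participant, one participant recoded across the Grade 3 boundary moves that arm's proportion by 1/30 = 3.3 percentage points. How many would be recoded cannot be derived from the article.

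**The case against.** The best defence is that 2.9.2 sets the grading rule for all events without exception, and 2.9.3 follows directly after it. The five-grade scale is then the natural source for Grade ≥3. The tiers of 2.10 stand in the monitoring-board section, and their brackets can be read as the response to each grade and not as its definition. Nothing says that they feed 2.9.3.

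This has force and makes the consequence conditional. It does not remove the inconsistency. Section 2.10 says that events were classified this way ("Adverse events were classified into four tiers per CTCAE v5.0 criteria"), and Case A remains under the milder reading, because the response attached to Grade 2 still conflicts with the no-intervention description in 2.9.3.

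A reader might infer more than the text supports:

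- **That the Grade ≥3 result will count stopping decisions.** The article does not say which scale is used.
- **That every mild reaction withdrawn under 2.7 becomes Grade 3.** Section 2.10 also asks for a consultation.
- **That such reactions fall mainly in the active arm.** Both arms have the skin cleaning, ear clips and electrode contact, and no rates by arm are given.
- **That deaths are lost.** Section 2.9.2 has a Grade 5 and lists death as a serious event. Only the 2.10 tiers lack a place for it.
- **That events after treatment cannot be graded.** Section 2.9.2 covers all events, and 2.9.1 includes this window: "Extended follow-up phase: T1 to T2 follow-up".
- **That the reporting times for serious events conflict.** A 12-hour limit for life-threatening events satisfies the 24-hour limit of 2.9.2.

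It is also fair that 2.9.3 specifies no between-arm test of Grade ≥3, and that its incidence formula, episodes over treatment sessions, does not depend on grade.

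**Conclusion.** The point holds as an inconsistency in the definition of grade. Sections 2.9.2, 2.9.3 and 2.10 cannot all be applied as written: the number of levels differs, 2.10 has no fatal tier, and the lower stratum of 2.9.3 excludes what 2.10 attaches to Grade 2.

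The effect on results is conditional. If the 2.10 tiers or the action wording of 2.9.3 are used for coding, the Grade ≥3 stratum would mix severity with management. If the 1–5 grade of 2.9.2 alone is used, it would not. The documents support no estimate of the number of events affected. They also do not support saying that the safety comparison is wrong in a particular direction.

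The change should be made. These are rules that the article states and that conflict with each other, not detail left to a fuller document.

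**What to change.** - Make the 1–5 CTCAE v5.0 severity grade of 2.9.2 the only adverse-event grade in 2.9.3 and 2.10, and in all three observation windows of 2.9.1.
- Define the Grade ≥3 stratum of 2.9.3 by that grade alone. Remove the action wording from both strata.
- Record action taken with the stimulation as a separate item (for example none, interrupted, terminated, or not applicable after treatment ends), and tabulate it by arm beside severity. The case report form may already hold this item; the article does not show it.
- Reconcile 2.7, 2.9.2, 2.9.3 and 2.10 so that any management text is labelled as management and does not define a grade. This does not require choosing or changing a clinical rule.

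The cost is wording in three sections and at most one form field, with no extra patients or visits. The article reports the first enrolment in July 2024, so any events already coded on the 2.10 tiers should be regraded by severity before the database is locked and the groups are unblinded.
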